**Figure 3 fig3:**
[figure not shown]
The rTMS measurement and intervention were performed on FS patients.

### Sham-rTMS

In control group C, Sham rTMS will be delivered with the coil angle rotated 90° and only one wing of the coil touching the scalp of the participant to avoid inducing actual stimulation. The sound emitted during stimulation, the time and frequency of the sham rTMS will be the same as intervention group A and B (43).

### Outcomes

Participants will be evaluated by physical therapists unaware of group assignments at various time intervals using the assessments detailed in Table 1. Furthermore, baseline age, gender, symptoms, duration, prior therapy, and frequently utilized medication will be documented via a questionnaire. The primary endpoint is the four-week duration, during which any side effects will be documented in real time.

### Clinical effectiveness

#### Primary outcome measures

The CMS is a typical shoulder function metric. Effective CMS implementation has shown its validity, reliability, and responsiveness in shoulder pathology identification (45). The minimal clinically important difference (MCID) considered for the score is 17 points (46). The CMS scale evaluates four dimensions associated with shoulder pathology: two subjective factors—pain and activities of daily living (ADL)—and two objective factors—ROM and strength. The CMS employs the presence or absence of “unaffected sleep” as a criterion for scoring shoulder function (47). The subjective components can receive up to 35 points and the objective 65, culminating in a total possible score of 100 points, with higher values indicating superior functionality (48).

### Secondary outcome measures

#### Polysomnography

Despite a robust correlation between sleep disruption and pain, shoulder complaints and sleep disturbances have been studied little. The patients will undergo single-night polysomnography examination in the special ward in rehabilitation medicine center in Seventh People’s Hospital of Shanghai University of Traditional Chinese Medicine using a Nox A1s™ (NoX Medical, Reykjavik, Iceland) device. Recording will occur between 10:00 p.m. and 6:00 a.m., depending on the patient’s preferences and sleep patterns. The polysomnographic examinations documented electroencephalography, electrocardiography, electrooculography, and electromyography recordings from the chin area and bilaterally from the masseter muscle regions, motion recording of abdominal and thoracic breathing activity, assessment of body position, and audio recording (Figure 4). A pulse oximeter (NONIN 3150 WristOx 2; Nonin Medical Inc., Plymouth, USA) will be used to record oxygen saturation and pulse, and Noxturnal™software (Nox Medical) for sleep recording and analysis will assist in data interpretation (49).

**Figure 4 fig4:**
[figure not shown]
Polysomnography were performed on FS patients.

#### 36-item short-form health survey (SF-36)

The 36-Item Short-Form Health Survey (SF-36, Chinese version) serves as the secondary outcome measure, functioning as a reliable and valid health-related questionnaire that measures QOL. The of 36 questions scale measures physical and mental health. The former encompasses physical, social, physical role, and emotional role functions. The latter contains mental health, energy fatigue, pain, and general health. The SF-36 scores range from 0 to 100, with higher scores indicating better QOL over the previous month (50).

### Neuro-biomechanism

#### Surface electromyography(sEMG)

Shoulder movements and muscle selection.

The participants performed shoulder movements including flexion, extension, abduction and upper limb coordinated movement “reach-to-grasp (RTG)” as the main basic shoulder movements and basic training processes in shoulder disfunction rehabilitation and also related to the frequent motions in ADL (51). The natural dropping state of the arm (shoulder resting state) will be added for a baseline recording of EMG signals. EMG signals from 8 muscles that control the movements of the upper arm will be recorded. Muscle names and the corresponding electrode numbers are shown in Table 2.

**Table 2 tab2:** The series number of the sEMG electrodes and the name of the muscle in which they are located.

Electrode number	Muscle	Electrode number	Muscle
1	Pectoralis Major	5	Middle Deltoid
2	Upper Trapezius	6	Posterior Deltoid
3	Supraspinatus	7	Bicep
4	Anterior Deltoid	8	Triceps

These 8 muscles will be measured using the 8-channel wireless EMG measurement system (iRecorder W8, Shanghai Idea-Interaction Tech. Co. Ltd., Shanghai, China) and eConScan data acquisition system (eConScan W8 BT, Shanghai, China). The Ag-Cl gel surface electrodes (Cathay, CH3236TD)will be used. The reference electrode will be placed on the lateral epicondylitis of humerus of the affected upper limb and the ground electrode will be placed at the inferior margin of the left sternal body adjacent to the xiphoid process. The sampling frequency will be set to 1,000 Hz. The skin will be wiped with 70% alcohol before electrodes placement. Shoulder EMG data will be collected in different groups using the following paradigms (51).

Paradigm 1 (Normal-speed and anti-gravity experiment): The participants will perform four kinds of shoulder movements: flexion, extension, abduction and RTG movement (drinking task with five phases: reaching to grasp a glass, forward transport of the glass to the mouth, drinking a sip of water, transporting the glass back to the table, returning the hand to the initial position) in the normal-speed without resistance just anti-gravity (Figure 5). A total of 80 EMG datasets will be collected for each participant, including 20 datasets for each movement. The action execution and collection interval are located between the two ends of the basic state interval. Resting state datasets will be collected from the baseline EMG signals for about 3 s before and after each movement. EMG baseline signal recording requires participants to relax and keep their arms at their sides.

**Figure 5 fig5:**
[figure not shown]
Four kinds of shoulder movements in sEMG measurement.

Paradigm 2 (Normal-speed and anti-resistence experiment): The participants will wear a 5-pound wristband on the affected upper limb. The experimental platform, the actions and datasets are the same as in paradigm 1.

### Data preprocessing

The original EMG signals collected by the EMG signal acquisition platform will be 8 channel EMG signals with a sampling frequency of 1,000 Hz. In order to obtain effective information in the EMG signals, and to filter out noise and artifacts, a band pass filter of 1 − 100hz will be selected. Due to the small value of the original EMG singal voltage collected, in which the order to reduce the loss value at the beginning of the iteration, we enlarged the original data by 1,000 times.

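### The fixed 1-100 Hz sEMG band pass lets movement artefact through and cuts muscle signal above 100 Hz, in a secondary outcome that serves Aim 2

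*Protocol article*

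**What the plan says.** The article gives the sampling rate twice, consistently. Under Surface electromyography: "The sampling frequency will be set to 1,000 Hz". Under Data preprocessing: "8 channel EMG signals with a sampling frequency of 1,000 Hz".

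Data preprocessing also fixes the filter and gives its purpose. The purpose has two parts: "In order to obtain effective information in the EMG signals", and "to filter out noise and artifacts, a band pass filter of 1" to an upper edge where "100hz will be selected".

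The recordings are dynamic. In Paradigm 1, "The participants will perform four kinds of shoulder movements: flexion, extension, abduction and RTG movement", the last being a five-phase drinking task. Paradigm 2 repeats the same actions under load: "The participants will wear a 5-pound wristband on the affected upper limb". Both paradigms are performed at normal speed. About 3 s of rest is recorded before and after each movement.

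The Abstract lists sEMG among the secondary outcomes, and Table 1 schedules it at all six assessments. Aim 2 relates clinical efficacy to neuro-biomechanism, and Data analysis plans Pearson correlation between primary and secondary outcomes.

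**The concern.** The filter is meant to keep useful EMG information and to remove noise and artefact. Both edges sit awkwardly with that.

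- **Lower edge.** Arm, electrode and cable movement during reaching and lifting would be expected to appear at a few hertz and somewhat above. A 1 Hz edge lies below that range.
- **Upper edge.** The system records up to 500 Hz, but everything above 100 Hz is removed, and no reason is given for doing so.

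What is at stake is the interpretation of the sEMG outcome. The Constant-Murley score includes range of motion and strength among its 65 objective points. If retained movement artefact changes as range of motion changes, part of an association between sEMG and the Constant-Murley score could reflect movement and not muscle activation. Randomisation would not remove this if one arm regained more motion than another. Separately, lost muscle signal may make the sEMG measures less sensitive.

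**Working it through.** **Inputs from the article.** Sampling rate fs = 1,000 Hz; filter edges 1 and 100 Hz; recordings during active movement.

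**Inputs assumed, because the article does not give them.** Movement artefact lies below about 20 Hz. The filter is a Butterworth design of order 2 or 4. The EMG power spectrum is S(f) = fh⁴f² / [(f² + fl²)(f² + fh²)²], with corner pairs fl/fh from 30/60 to 100/200 Hz.

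The article states no figure for retained or discarded signal, so there is none to reproduce.

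**Step 1: bandwidth.** The highest frequency that can be recorded is fs/2 = 1,000/2 = 500 Hz. The filter keeps (100 − 1)/500 = 99/500 = 19.8% of that range. This is a share of hertz, not of muscle signal.

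**Step 2: what the lower edge does.** Gain of a 1-100 Hz Butterworth band pass at fs = 1,000 Hz:

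| Frequency (Hz) | Order 2 | Order 4 |
|---|---|---|
| 0.5 | 0.24 | 0.06 |
| 1 | 0.71 | 0.71 |
| 2 | 0.97 | 1.00 |
| 5 | 1.00 | 1.00 |
| 10 | 1.00 | 1.00 |
| 20 | 1.00 | 1.00 |

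Content well below 1 Hz is cut. Content from 2 to 20 Hz is essentially untouched.

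**Step 3: what the upper edge does.** Integrating S(f) over each band and dividing by its integral over 0-500 Hz gives these shares of EMG power:

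| Corners fl/fh (Hz) | Kept by 1-100 Hz | Lost above 100 Hz | Lost below 20 Hz | Kept by 20-450 Hz |
|---|---|---|---|---|
| 30/60 | 87% | 13% | 10% | 90% |
| 40/80 | 76% | 24% | 4.9% | 95% |
| 60/120 | 53% | 47% | 1.6% | 98% |
| 80/160 | 36% | 64% | 0.7% | 98% |
| 100/200 | 25% | 75% | 0.4% | 98% |

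The column for loss below 20 Hz is what a 20 Hz lower edge would give up. The stated filter loses 13-75% of EMG power, depending on the spectrum. The 20-450 Hz band keeps more in every row, but at the lowest corners the difference is only 90% against 87%.

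**Step 4: artefact size.** The article has no data on the amplitude of movement artefact, so the net effect on any sEMG measure cannot be computed.

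**The case against.** The strongest reply is that the fault depends on premises from outside the article, which gives neither the EMG spectrum nor the movement band. Sampling faster than the analysis band is ordinary and contradicts nothing. That stands as a limit on the size of the effect, and it is why the power loss is shown as a range. It does not rescue the lower edge: the article itself gives artefact removal as the purpose and describes active movement, and a 1 Hz edge removes little except drift.

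Several stronger readings are tempting but not supported:

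- **That four fifths of the muscle signal is thrown away.** The 80% is bandwidth. Under the assumed spectra, 25-87% of the power is kept.
- **That the filter works against its purpose altogether.** It does remove drift below 1 Hz and noise above 100 Hz.
- **That mains interference is left untreated.** The article mentions no notch filter, but a journal article may leave this to the full protocol, so it is not part of this point.
- **That recovering patients move faster and so generate more artefact.** Both paradigms are set at normal speed. Range of motion can still change.
- **That a frequency or activation measure is distorted.** The article does not define the sEMG endpoint. Its remark about loss value during iteration hints at an iterative model, so the effect on a particular summary cannot be asserted.

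It is also fair to say that one rule applies to every arm and visit, that sEMG is one of several secondary outcomes, and that the setting can be reversed if raw recordings are kept. These points limit the severity. They are not a reason to keep the band edges.

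**Conclusion.** The point holds for the two stated band edges. The lower edge passes movement artefact at nearly full gain (0.97-1.00 from 2 to 20 Hz), so the filter does not do that part of its job. The upper edge discards an estimated 13-75% of EMG power that the recording could have held.

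The first result rests on movement artefact lying mostly below about 20 Hz and on a Butterworth-type filter; the second rests on the assumed spectra. The size and direction of any bias in the sEMG results, or in their correlation with the Constant-Murley score, are unknown.

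The primary outcome and the sample size are not affected. This is a change that should be made to a secondary outcome, not a threat to the trial's main conclusion.

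**What to change.** Before the sEMG data are analysed, change the passband so that it starts above the movement band and ends below 500 Hz. A 20-450 Hz band is one example; it is a conventional choice and is not derived from the article. Apply the same setting to the stored raw 1,000 Hz signals from all arms and visits, and report the 1-100 Hz version as a sensitivity analysis. If there is a specific reason for 1-100 Hz, such as the needs of a particular model, state it.

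The cost is one processing setting, provided the raw signals have been kept. Any signals already filtered must be reprocessed. A 20 Hz lower edge also gives up the EMG power below 20 Hz, about 0.4-10% under the assumed spectra.

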### Motor evoked potential (MEP)

The peak-to-peak amplitude of the MEP of the FDI will be quantified as an indicator of motor evoked potential, indicating that magnetic stimulation over M1 (43) induces excitability in the descending route and contralateral muscle contraction of the recorded value. The M1 hotspot on the contralesional side of the FDI muscle will record 10 averaged MEPs at 120% of the baseline resting motor threshold. The identical stimulator output will be utilized for ensuing assessment sessions (52).

### Magnetic resonance imaging (MRI)

The MRI scan will utilize a 3.0-T GE scanner (Siemens Healthcare, Erlangen, Germany) equipped with an eight-channel phased-array head coil at the Department of Radiology of Seventh People’s Hospital of Shanghai University of Traditional Chinese Medicine, China. Each participant will get two independent brain MRI scans by two radiologists at baseline, after the 4-week intervention, and at the 6-month follow-up. The MRI will need participants to stay awake with their eyes closed.

Resting-state functional MRI (Rs-fMRI) images will be obtained using the subsequent parameters: TR = 2,100 ms, TE = 30 ms, flip angle = 90°, voxel dimensions = 3.125 mm × 3.125 mm × 3.6 mm, 42 axial slices, field of view (FOV) = 200 mm × 200 mm, and 230 phases. A 3D-BRAVO sequence with the following parameters will acquire high-resolution T1-weighted structural images (T1WI): TR = 8.2 ms, TE = 3.2 ms, flip angle = 12°, FOV = 220 mm × 20 mm, matrix = 256 × 256, slice thickness = 1 mm. The MRI results encompass GM density, WM, subcortical nuclei volumes, cortical thickness and FC. The DPARSF (http://rfmri.org/DPARSF) will preprocess fMRI data (53), while the FSL 5.0 (FMRIB Software Library) will analyze T1WI structural data (54). The volumes of neo-cortical gray matter, total gray matter, and white matter will be acquired using SIENAX, a component of FSL 5.0 (55). FMRIB’s integrated registration and segmentation tool in FSL 5.0 will calculate subcortical nuclei’s normalized volumes (56). Cortical thickness will be measured via FreeSurfer.

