Aim 1: To evaluate the efficacy of NMES combined with rTMS over the contralateral M1 area in reducing pain intensity and improving functional ability in patients with FS. And to compare the efficacy of LF-rTMS+NMES and HF-rTMS+NMES in patients with FS.

Aim 2: To investigate the correlation between the clinical efficacy and neuro-biomechanism of cortical alternation in patients with FS after conducting systematic evaluations both before and after treatment.

Aim 3: Based on this study protocol and its anticipated outcomes, clinicians can develop innovative management strategies for pain and motor function in patients with FS, aiming to achieve effective therapeutic results.

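### Gray and white matter volumes at three visits come from a tool that segments each scan on its own, although Aim 2 needs change within the patient

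*Protocol article*

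**What the plan says.** All of this is in the protocol article; no separate analysis plan is shown.

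- **Aim 2** (Introduction) is to relate clinical efficacy to "cortical alternation in patients with FS after conducting systematic evaluations both before and after treatment".
- **Table 1** places MRI at baseline, 4 weeks and the 6-month follow-up.
- **Data analysis** plans Pearson correlations between primary and secondary outcomes.
- **MRI section, tools.** For global tissue volumes: "The volumes of neo-cortical gray matter, total gray matter, and white matter will be acquired using SIENAX, a component of FSL 5.0". Subcortical nuclei use a separate FSL tool, functional data are preprocessed in DPARSF, and for the cortex: "Cortical thickness will be measured via FreeSurfer".
- **MRI section, outcomes.** The list includes GM density, and the Table 1 legend repeats it. The processing steps then described give volumes and thickness.
- **MRI section, number of scans.** Each participant has two independent scans, involving two radiologists, at each of the three time points. How the two are combined is not said.
- **MRI section, acquisition.** The scanner line reads "The MRI scan will utilize a 3.0-T GE scanner (Siemens Healthcare, Erlangen, Germany". The T1 structural line reads "FOV = 220 mm × 20 mm, matrix = 256 × 256, slice thickness = 1 mm".

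**The concern.** Aim 2 and the three MRI visits call for change within a patient. SIENAX estimates a head-size-normalised volume from a single scan. That is what the named method does; the article itself does not spell it out. When two such volumes are subtracted, the errors of both scans enter the change in full.

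Structural change over 4 weeks may well be small. Random error in it widens the interval for any difference between arms and weakens the observed correlation with CMS, so a real relation could be missed. Processing a patient's scans jointly is designed to reduce this error, and FreeSurfer, which offers such a stream, is already in the plan.

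Three smaller faults stand in the same section. One scanner is given two makers. The T1 field of view is impossible as printed. One listed outcome, GM density, has no named step that produces it.

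**Working it through.** **1. The plan's own figure, to fix the number per arm.** The plan has no sample size or error figure for MRI. Its only calculation is for CMS: f = 0.25, 3 groups, 6 measurements, correlation 0.5, alpha 0.05.

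- λ = f²·N·m / (1 + (m − 1)ρ) = 0.0625 × 93 × 6 / 3.5 = 9.96, with 2 and 90 degrees of freedom. Power is 0.8001, so 93 reproduces.
- 93 / 0.8 = 116.25, rounded up to 117, or 39 per arm.
- Evaluable number per arm: 93 / 3 = 31.

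**2. Precision of a between-arm difference in change, error part only.** Let e be the error SD of one scan, as a percentage of volume. This is an assumption, shown as a range.

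- Error variance of a change: 2e².
- Half-width for a difference between two arms of 31: 1.96 × e × √2 × √(2/31) = 0.704e.
- If two scans per visit are averaged and their errors are independent, divide by √2.

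| Assumed e | One scan per visit | Two scans averaged |
|---|---|---|
| 0.5% | 0.35% | 0.25% |
| 1% | 0.70% | 0.50% |
| 2% | 1.41% | 1.00% |

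True variation in change between patients comes on top, so the full interval is wider than this.

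**3. Attenuation of the correlation with CMS.** Let s be the SD of true change (assumed) and k the scans averaged per visit. Reliability is R = s² / (s² + 2e²/k), and a true correlation is multiplied by √R.

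| e | s | k | R | √R |
|---|---|---|---|---|
| 0.2% | 1.0% | 1 | 0.93 | 0.96 |
| 0.2% | 1.0% | 2 | 0.96 | 0.98 |
| 0.5% | 0.5% | 1 | 0.33 | 0.58 |
| 0.5% | 0.5% | 2 | 0.50 | 0.71 |
| 1.0% | 0.3% | 1 | 0.04 | 0.21 |
| 1.0% | 0.3% | 2 | 0.08 | 0.29 |

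The loss runs from negligible to severe, depending on inputs that the documents do not give.

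**4. Scan geometry.**

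- T1, from "FOV = 220 mm × 20 mm, matrix = 256 × 256": 220/256 = 0.859 mm by 20/256 = 0.078 mm, an 11:1 pixel. A 20 mm field cannot cover a brain.
- Resting-state fMRI, from "voxel dimensions = 3.125 mm × 3.125 mm × 3.6 mm, 42 axial slices, field of view (FOV) = 200 mm × 200 mm": 200/3.125 = 64 exactly, and 42 × 3.6 = 151 mm of coverage. This line is coherent, so the fault is confined to the T1 line.

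**The case against.** The strongest reply is that a condensed article may leave processing detail to the full protocol or an imaging manual. This stands for cortical thickness: naming FreeSurfer does not exclude its longitudinal stream. It does not remove the point for gray and white matter, where the article positively fixes a one-scan tool.

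A second reply is that no size is established. That stands. Both e and s are assumptions, and averaging the two scans per visit, if that is intended, reduces the error.

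A third reply is that error of equal size in all arms costs precision and creates no false treatment effect. That also stands.

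A reader might infer more than the documents support:

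- *Measurement error will swamp the cortical change.* This holds only at one end of the assumed range and is absent at the other.
- *All MRI outcomes rest on a single-scan tool.* SIENAX covers only global gray and white matter volumes. Functional connectivity is outside the argument.
- *Joint processing would be worth about four times the sample size.* That presumes the error is halved, for which the documents give no figure, and it concerns the error part alone.
- *Scanners of two makers are in use, so a switch could mimic change.* The text names one scanner in one department. The two makers and the 20 mm figure look like reporting slips and do not themselves show added measurement error.

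On GM density, FSL is named generally for the structural data, so a density step is not ruled out. None is specified, however.

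**Conclusion.** The point holds in a limited form. For gray and white matter volumes the plan names a method that segments each scan separately, while Aim 2 needs within-patient change. The result is avoidable noise in a secondary structural outcome and a correlation with CMS biased toward zero.

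The half-widths in step 2 of the working indicate scale only. They rest on assumed per-scan errors of 0.5–2%, on 31 evaluable patients per arm, and, for the lower set, on independent errors of two averaged scans. The documents do not allow the actual loss to be calculated.

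The contradictory maker, the impossible T1 field of view and the unmatched GM density outcome are minor but real. The acquisition cannot be reproduced from the text as it stands. The primary CMS analysis and the sample size are not touched. This is a cheap improvement to make, not a threat to the trial's main conclusion.

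**What to change.** In the MRI section:

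1. For change from baseline, process each patient's scans together with the FreeSurfer longitudinal stream (within-subject template). Use it for gray matter, white matter and subcortical volumes and for cortical thickness. SIENA may be added for whole-brain change, but it would not by itself replace the separate gray and white matter measures. Keep SIENAX for describing baseline.
2. State how the two scans per visit are used: averaged, one chosen by a stated rule, or one acquisition read twice.
3. Reconcile the scanner's maker and correct the T1 field of view from the scanner's own protocol. A 220 mm × 220 mm field would give 0.859 mm pixels, but the investigators must confirm the true value.
4. Name the tool that yields GM density, or replace that outcome, here and in the Table 1 legend, with the volumes and thickness actually produced.

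The cost is longer computing time and corrected text. No extra scans are needed, and processing can be changed on stored images although recruitment has begun. A patient with only one usable scan contributes no change value.
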